## Abstract

**Background:**

Acute allograft rejection is a major cause of early mortality in the first year after heart transplantation in adults. Although endomyocardial biopsy (EMB) is not a perfect "gold standard" for a correct diagnosis of acute allograft rejection, it is considered the best available test and thus, is the current standard practice. Unfortunately, EMB is an invasive and costly procedure that is not without risk. Recent evidence suggests that acute allograft rejection causes delays in ventricular repolarization and thereby increases the cellular action potential duration resulting in a longer QT interval on the electrocardiogram (ECG). No prospective study to date has investigated whether such increases in the QT interval could provide early detection of acute allograft rejection. Therefore, in the Novel Evaluation With Home Electrocardiogram And Remote Transmission (NEW HEART) study, we plan to investigate the potential benefit of daily home QT interval monitoring to predict acute allograft rejection.

**Methods/design:**

The NEW HEART study is a prospective, double-blind, multi-center descriptive research study. A sample of 325 adult heart transplant recipients will be recruited within six weeks of transplant from three sites in the United States. Subjects will receive the HeartView™ ECG recorder and its companion Internet Transmitter, which will transmit the subject's ECG to a Core Laboratory. Subjects will be instructed to record and transmit an ECG recording daily for 6 months. An increase in the QT_C _interval from the previous day of at least 25 ms that persists for 3 consecutive days will be considered abnormal. The number and grade of acute allograft rejection episodes, as well as all-cause mortality, will be collected for one year following transplant surgery.

**Discussion:**

This study will provide "real world" prospective data to determine the sensitivity and specificity of QT_C _as an early non invasive marker of cellular rejection in transplant recipients during the first post-transplant year. A non-invasive indicator of early allograft rejection in heart transplant recipients has the potential to limit the number and severity of rejection episodes by reducing the time and cost of rejection surveillance and by shortening the time to recognition of rejection.

**Trial Registration:**

ClinicalTrials.gov: NCT01365806

## Background

The prevalence of American adults living with a heart transplant was 20,369 in 2009, the most recent year for which complete data are available [1]. Acute allograft rejection is a major cause of early mortality, a rate that reaches 13% in the first year after heart transplantation in adults [1,2]. According to the 2011 annual United States data published from the International Society for Heart Lung Transplantation Registry, 26% of heart transplant recipients have at least one rejection episode within the first year following transplant surgery [2]. Acute rejection remains the most common cause of morbidity and rehospitalization. Jalowiec [3] reported that 64% of heart transplant recipients were rehospitalized during the first year after transplant surgery (median length of stay, 16 days), and 37% were rehospitalized more than once. Rejection is also a primary cause of urgent re-transplantation, a situation that is perceived by some to be morally unfair because these patients are allowed a second transplant while others are waiting and often dying before receiving their first transplant. Thus, the financial, physical, and emotional toll associated with acute rejection is significant.

In order to detect the early stages of rejection so that more aggressive and early immunosuppressant therapy can be initiated, frequent biopsies of heart tissue are performed (typically, weekly or every other week in the first three months and then monthly or every other month during the first year). Although endomyocardial biopsy (EMB) is not a perfect "gold standard" for a correct diagnosis of acute allograft rejection, it is considered the best available test and thus, it is the current standard practice. Unfortunately, EMB is an invasive and costly procedure that is not without risk [4,5]. If a simple noninvasive biomarker could be identified to detect the early stages of acute rejection, it might be possible to reduce the number of invasive biopsy procedures and to initiate earlier therapy that might prevent death from severe rejection.

Alternatives to invasive EMB monitoring have been the subject of recent study. Most prominently, the use of a commercially available test, the AlloMap, that determines gene-expression profiling of recipient leukocytes, was tested against routine EMB to determine whether adverse events (a composite of allograft dysfunction, death, or retransplantation) differed between patients who received standard EMB monitoring and those who received monitoring by gene-expression profiling [6]. Although the authors concluded that the gene-expression profiling was not inferior to EMB in its association with adverse events, only 6 of 34 rejection episodes in the AlloMap group were identified solely on the basis of the profiling test [6]. Further, the wide confidence intervals for adverse events translated into as much as a 68% increase in risk with AlloMap monitoring [7]. Most participants were randomized more than one year after transplant, which limits the generalizability of these findings to the higher risk, early (< one year) post-transplant group that we propose to study.

Other investigators have focused on the electrocardiogram (ECG) as a potential marker of allograft rejection because it is noninvasive and easily measured. Previous studies have investigated the QT interval, an indirect measure of the cellular action potential duration of ventricular myocytes. The QT interval, defined as the interval from the beginning of the QRS complex to the end of the T wave, reflects the time that elapses between the initial fast depolarization of the ventricles and their subsequent repolarization. Recent evidence suggests that acute allograft rejection causes delays in ventricular repolarization and thereby increases the cellular action potential duration resulting in a longer QT interval on the ECG [8-12]. Findings from two studies suggest that the QT interval is linked to acute allograft rejection and three other studies have linked an increased QT interval with mortality (Table 1). However, these studies all have serious limitations. All but one were retrospective analyses. All involved hospital or clinic-acquired ECGs, typically done at baseline seven days following transplant surgery and then annually or at the time of hospitalization for acute severe allograft rejection. Thus, none of the studies could report whether QT interval prolongation was an early sign of rejection or simply the result of severe, irreversible rejection. Another limitation was that all but one study made no mention of investigators being blinded from clinical information about allograft rejection. Thus, it is possible that the researchers making manual measurements of the QT interval were biased by knowing whether the subject did or did not have acute allograft rejection. Despite these limitations, there is evidence that an increase in the QT interval is linked to acute allograft rejection and mortality.

**Table 1 T1:** Human Studies on QT Interval Prolongation after Heart Transplantation

# Subjects Author/Yr	Study Design	Major Findings	Study Limitations	Implications for NEW HEART Study
N = 65 Richartz et al. 1998 [8]	Prospective; Rejection during in-hospital period	1. Mean QT_C _= 449 ± 2 ms without rejection; 517 ± 11 ms with rejection (*p *< 0.001) 2. > 10% increase in QT_C _predicted rejection with sensitivity, 86%; specificity, 88%	1. Only observed rejection during hospitalization for transplant surgery 2. Analyzed only 3 ECGs per subject 3. ECG analyzers not blinded from clinical information about rejection	An increase in the QT interval predicts acute allograft rejection

N = 52 Kolasa et al. 2005 [9]	Retrospective; Long-term mortality over 7 yrs	Poorer survival over 7 yrs in subjects who had a > 10 ms per year change in their QT_C _interval on their annual ECG	1. Link to rejection not studied 2. Analyzed only one ECG per year	As little as a 10 ms change in the QT interval is linked to mortality

N = 200 Tenderich et al. 2006 [10]	Retrospective; Rejection during first 3 months	> 25 ms increase in QT_C _interval predicted acute allograft rejection with sensitivity, 77%; specificity, 96%.	1. Only analyzed 2 ECGs per subject 2. ECG analyzers not blinded from clinical information about rejection	Increase in QT interval predicts acute rejection during the period of interest

N = 587 Vrtovec et al. 2006 [11]	Retrospective; Long-term mortality up to 17 yrs	1. Patients with ≥ 10% increase in QT_C _interval between 1^st ^and 2^nd ^year post-transplant had 6.86 times higher risk of dying.2. ≥ 10% increase in QT_C _was the only independent predictor of long- term mortality on multivariate analysis 3. Trend was a decreasing QT_C _over the yrs suggesting sympathetic reinnervation	1. Link to rejection not studied 2. Analyzed only one ECG per year	An increase in the QT interval is linked to mortality

N = 71 Vrtovec et al. 2008 [12]	Retrospective; 1- year all-cause & SCD mortality in subjects with severe acute rejection	1. QT_C _was longer in SCD group than in survivors (475 ± 57 versus 437 ± 36 ms; *p *= 0.02) 2. Patients who had > 10% increase in QT interval during a severe acute rejection episode were at increased risk for SCD.	1. Limited to just patients with severe rejection; unable to tell whether increased QT interval could predict earlier, milder forms of rejection 2. Analyzed just 2 ECGs per subject (one at baseline 7 days after surgery, second at time of rejection)	An increase in the QT interval is linked to mortality

ms = millisecond; SCD = sudden cardiac death; QTc = QT interval corrected for heart rate

No prospective study to date has investigated whether such increases in the QT interval could provide early detection of acute allograft rejection. In addition, advances in home ECG monitoring have evolved and become less cumbersome and more patient-friendly. Therefore, in the Novel Evaluation With Home Electrocardiogram And Remote Transmission (NEW HEART) study, we plan to take advantage of novel ECG technology to investigate the potential benefit of daily home QT interval monitoring to predict acute allograft rejection following heart transplantation.

## Methods/design

### Design

The NEW HEART study is a prospective, double-blind, multi-center descriptive research study. The primary aims of the NEW HEART study are to: 1) determine whether an increase in the QT interval during the first 6 months following heart transplant is a sensitive and specific biomarker for acute allograft rejection; 2) determine the timing of initial increased QT interval relative to biopsy-diagnosed stages of mild, moderate, and severe allograft rejection.

Secondary aims are to: 1) determine whether an increase in the QT interval during the first 6 months following heart transplant predicts mortality within the first year, and 2) explore additional ECG measurements that might predict acute allograft rejection or death.

### Sample

A sample of 325 adult heart transplant recipients will be recruited from the Columbia University-New York Presbyterian Medical Center (CU-NYP), the University of California, Los Angeles (UCLA), and Cedars Sinai Medical Center (CSMC) in Los Angeles, CA. Respectively, demographic characteristics at these sites are: male (68.9%, 75.7%, and 79.7%); White (53.1%, 59.1%, 73.4%); Black (20.3%, 9.4%,12.5%); Latino (14.5%, 19.9%, 9.4%) and Asian (11.3%, 10.5%, 3.1%) [1]. Inclusion criteria are: 1) ≥ 18 years of age, 2) first heart transplant surgery within six weeks of their transplant surgery, 3) not enrolled in other research studies that conflict with the study design, 4) clinically stable at time of enrollment (i.e. no clinical symptoms of allograft impairment with ejection fraction ≥ 45%).

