### Procedures

Participants will be recruited either while they are in the hospital for transplant surgery, or if that is inconvenient, during their first clinic visit following transplant surgery. After informed consent is obtained, demographic and clinical data will be collected by self-report and by medical record audit. At the time of each EMB, data from the medical record will be abstracted to confirm current medications, serum levels of anti-rejection medications, clinical data regarding EMB results, and other clinical data reflecting myocardial performance consistent with rejection status. Only one anti-rejection medication (tacrolimus) is associated with an increased QT interval. If a patient is on chronic tacrolimus therapy without a change in dosage, it should not interfere with the daily ECG monitoring measurement because we will be comparing each patient with him/herself and noting any change from the previous day's QT interval. However, we will track initiation or change in any QT-prolonging drug. On their website, the Arizona Center for Education and Research on Therapeutics [15] maintains a comprehensive list of QT- prolonging drugs that we have incorporated into the medications section of our electronic database system. Further, on a quarterly basis, we will continue to reference this website for new drugs as they come to market and update our data capture to include those associated with QT-prolongation.

The other drug class that patients may be taking is 3-Hydroxy-3-Methyl-Glutaryl Coenzyme A Reductase inhibitors (i.e., statins) which are known to shorten the QT interval. Thus, we will also monitor statin therapy. To insure patient safety, we will notify patients' transplant cardiologists within 48 h of the detection of any QTc interval exceeding the population 99th percentile for adult males (> 470 ms) or females (> 480 ms) [16].

At the time of informed consent and enrollment, subjects will receive the HeartView™ recorder and its companion Internet Transmitter, which will transmit the subject's ECG as described earlier. Subjects will be asked to record a 10-s 8-lead ECG daily for 6 months.

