### Analysis of ECG monitoring data

The ECG will be sent to a large server hosted by the UCSF Office of Academic and Administrative Information Systems (OAAIS). The server is a secure, highly redundant data center with 24/7 availability due to back-up generators that protect against power outages. The system provides nightly data backup. Investigators in the [name] Lab will access the ECG data by logging on with a username and password via a Virtual Private Network (VPN), which encapsulates data transfers between networked devices not on the same private network and keeps the transferred data private from other devices. Investigators who analyze the daily ECG data will be blinded from all information regarding the subject's clinical status and biopsy results. In addition, pathologists who grade the biopsies and clinicians who provide medical care in the transplant clinics will be blinded from the QT interval monitoring data.

QT and RR intervals will be made in a computer-assisted manner. The Aerotel measurement software provides a zooming feature to enlarge ECG waveforms for better visualization. In addition, electronic calipers are provided so that the researcher will select the appropriate waveform onset and offset points and the computer software will provide the interval value in milliseconds (ms). The QT interval will be measured from the onset of the QRS waveform to the end of the T waveThe end of the T wave will be defined as the intersection of a tangent to the steepest slope of the last limb of the T wave and the baseline (Figure 2) [18]. A standardized correction to account for the effect of HR will be applied (QT_C_). An increase in the QT_C _interval from the previous day of at least 25 ms that persists for 3 consecutive days will be considered abnormal [10].

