### Diagnosis of acute allograft rejection

Rates of acute allograft rejection have varied, but the most recent rates of rejection in the first 6 months after transplant are reported to be 25 to 35% [2]. The diagnosis of acute allograft rejection is made by an EMB which will be performed in the hospital cardiac catheterization laboratory at each site. Generally, 3-6 biopsy specimens of the right ventricular endocardium are taken to minimize false negative tests. Each site will follow its own acute rejection surveillance protocol. In general, these protocols require weekly or biweekly EMBs during the first two to three post-transplant months. After that time, biopsies are performed less frequently, based on clinical judgment and risk of rejection. At each site, EMBs will be graded by clinical pathologists experienced with the heart transplant population and using the International Society of Heart and Lung Transplantation standards for acute rejection. Although early reports indicated inter-operator variability in the interpretation of EMB results [22], the use of the standardized grading system has improved the reliability and validity of the measurement. Current variability in interpretation of biopsy results occurs mainly in the diagnosis of Grade 2 rejection by local pathologists which may be misinterpreted in the presence of endocardial infiltrates called Quilty lesions [23,24]. To control for potential variability, we will monitor and record clinical and hemodynamic indicators of myocardial performance, which are obtained at the time of each biopsy or at regular clinical assessments, to support the biopsy interpretation, particularly regarding Grade 2 rejection. Such a multi-factorial approach to identification of rejection has been recommended [24].

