### Statistical analysis

Using the variable definitions in Table 2, a logistic regression analysis will be performed with the independent variable being presence/absence of the ECG criteria (ΔQT_C _≥ +25 ms × 3 days [10]) and the dependent variable being presence/absence of acute allograft rejection. Odds ratios and confidence intervals will be reported as well as the universal proportions used to determine the value of new diagnostic criteria (sensitivity, specificity, positive/negative predictive value, and predictive accuracy, Table 3).

**Table 2 T2:** Variable definitions for statistical analysis

Variable	Definition	Type of Variable
ΔQT_C_	≥ +25 ms increase in QT_C _interval from previous day lasting 3 consecutive days [10]	Continuous (expected range, 10-100 ms)

Acute allograft rejection	EMB category 1R or 2R or 3R with confirmation by treating physician	Categorical; dichotomous (yes/no) No = 0; Yes = 1R or 2R or 3R

Days to rejection	Number of days from first positive ECG criterion to mild, moderate, or severe rejection diagnosis. If the ECG criterion follows rejection, a negative # of days will be reported.	Continuous (expected range -365 to +365)

Acute rejection severity	EMB category: 1R (mild), 2R (moderate), 3R (severe)	Categorical

Cardiac rhythm	Sinus rhythm, atrial fibrillation, atrial flutter, junctional rhythm	Categorical

Heart rate	Heart rate per minute calculated from 30 s rhythm strip	Continuous (expected range, 60-120)

P wave duration	Interval from beginning to end of P wave in ms (measure of intra-atrial conduction delay)	Continuous (expected range, 70-126 ms)

QRS duration	Interval from beginning to end of the QRS waveform	Continuous (expected range, 72-160 ms)

PR interval	Interval from the beginning of the P wave to the beginning of the QRS complex measured in ms. PR interval > 200 ms indicates an abnormal delay of conduction (1^st ^degree AV block).	Continuous (expected range, 112-240 ms)

QRS amplitude	Height of QRS waveform in μV	Continuous (expected range, 500-1000 μV

T_PEAK _- T_END_	Interval from the peak of the T wave (or nadir in inverted T waves) to the end of the T wave in ms. Prolonged T_PEAK _-T_END _indicates heterogeneity of repolarization and risk for arrhythmia	Continuous (expected range, 112-240 ms)

**Table 3 T3:** Definitions of Universal Proportions

Criterion	Definition
Sensitivity	Proportion of those with acute rejection who are positive for the ECG criterion

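### Patients already in biopsy-proven rejection at the first ECG can enter and sit in the sensitivity denominator of a test that registers only a new QTc rise

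*Protocol article*

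**What the plan says.** All references are to the protocol article.

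- **Entry (Sample).** Of the four inclusion criteria, one concerns graft status: "clinically stable at time of enrollment (i.e. no clinical symptoms of allograft impairment with ejection fraction ≥ 45" per cent. Another sets the time limit: "first heart transplant surgery within six weeks of their transplant surgery". No biopsy finding is part of entry.
- **Biopsies around entry (Diagnosis of acute allograft rejection).** Sites follow their own surveillance schedules, but in general "these protocols require weekly or biweekly EMBs during the first two to three post-transplant months".
- **Start of monitoring (Procedures).** "At the time of informed consent and enrollment, subjects will receive the HeartView™ recorder and its companion Internet Transmitter". There are no study home ECGs before that.
- **Index test (Analysis of ECG monitoring data).** The test is an increase in the QTc "interval from the previous day of at least 25 ms that persists for 3 consecutive days will be considered abnormal".
- **Reference standard (Statistical analysis, Table 2).** Rejection is "EMB category 1R or 2R or 3R with confirmation by treating physician".
- **Clock (Follow-up and end-points).** Rejection episodes are collected over the year that starts at surgery, not at enrolment or the first ECG.
- **Accuracy measures (Statistical analysis, Tables 2 and 3).** Sensitivity is the share of patients with rejection who are ECG-positive. No time window links the ECG to the biopsy. An ECG criterion that comes after rejection is kept and given a negative number of days.

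**The concern.** Entry and outcome use different yardsticks. Stability is judged on symptoms and ejection fraction; rejection is judged on biopsy and includes the mild grade. The Background says that biopsies are done to find rejection in its early stages, so absence of symptoms does not rule out a positive biopsy.

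Take a symptom-free patient with adequate ejection fraction whose latest biopsy before enrolment is 1R and whose next biopsy, under daily ECGs, is again 1R. If confirmed, the patient is rejection-positive. If QTc rose when that episode began, as the study hypothesises, the rise came before the first recording. The criterion compares each day with the day before and has no pre-rejection baseline, so it cannot recover that rise. Restricting rejections to the monitored period does not help, because the second biopsy lies inside it.

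Both primary aims are touched. Aim 1 asks whether a QTc increase is a sensitive marker; aim 2 asks when it appears relative to each stage of rejection. The Background faults earlier studies because they could not tell an early sign from a consequence of established rejection. Mixing in episodes with unobserved onset brings part of that weakness back.

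**Working it through.** The article gives no calculation on this point, so there is no figure to reproduce. The check is an illustrative dilution.

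**Inputs**

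- Number of patients: "A sample of 325 adult heart transplant recipients will be recruited" (Sample).
- Rejection in the first 6 months: 25 to 35% (Diagnosis of acute allograft rejection). I assume this rate applies to the Table 2 definition.
- Sensitivity 77% and specificity 96% for a rise above 25 ms (Table 1, the retrospective study of 200 patients that is cited for the cut-off). I take 77% as the true sensitivity for new episodes.
- *f*, the share of rejection patients whose only episode was already present at the first ECG. It is not in the article; assumed 10, 20 or 30%.
- *q*, the chance that such a patient meets the ECG criterion at some later time. It is not in the article; assumed 0, 0.04 (one minus the 96% specificity), 0.40 or 0.77.

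**Observed sensitivity** = 0.77 × (1 − *f*) + *q* × *f*

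| *f* | *q* = 0 | *q* = 0.04 | *q* = 0.40 | *q* = 0.77 |
|---|---|---|---|---|
| 10% | 69.3% | 69.7% | 73.3% | 77% |
| 20% | 61.6% | 62.4% | 69.6% | 77% |
| 30% | 53.9% | 55.1% | 65.9% | 77% |

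Example: *f* = 0.20 and *q* = 0.40 give 0.77 × 0.80 + 0.40 × 0.20 = 0.616 + 0.080 = 0.696.

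**Comparison with sampling error.** Expected rejection patients are 325 × 0.25 = 81 to 325 × 0.35 = 114. The 95% half-width is 1.96 × √(0.77 × 0.23 / cases), which is 9.2 points at 81 cases and 7.7 points at 114. At *f* = 10% the loss is 77 − 69.3 = 7.7 points with *q* = 0, about the size of that half-width. With *q* = 0.40 it is 77 − 73.3 = 3.7 points, less than half of it or thereabouts.

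**Negative predictive value**, at 30% rejection and 96% specificity:

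- Sensitivity 77%: 0.672 / (0.672 + 0.30 × 0.23) = 91%.
- *f* = 20%, *q* = 0: 0.672 / (0.672 + 0.30 × 0.384) = 85%.
- *f* = 20%, *q* = 0.40: 0.672 / (0.672 + 0.30 × 0.304) = 88%.

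**What the table does not show.** At *q* = 0.77 the sensitivity looks untouched, but the prevalent patients counted as true positives owe that to a rise after the episode was already established. The number is the same; it does not describe early detection.

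**The case against.** A reader might infer that every patient in rejection at entry becomes a missed case, and that sensitivity will fall to between 54 and 69%. The article does not support that. Table 3 works per patient without a time window, and Table 2 keeps an ECG criterion that follows rejection. Any qualifying rise in six months, from whatever cause, makes such a patient a true positive. The 54 to 69% range needs *q* = 0, the worst case, together with an assumed *f*.

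Other objections also carry weight:

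- Procedures puts recruitment during the transplant admission, or otherwise at the first clinic visit. Six weeks is an outer limit, so few biopsies may precede the first ECG in many patients. Physician confirmation may remove further cases. Both would make *f* smaller.
- The 77% comes from a retrospective study with two ECGs per patient, not from daily recordings.
- A 1R at entry can progress to 2R or 3R under monitoring with a new, detectable rise. Discarding such a patient until a grade 0 biopsy is seen would lose information that aim 2 needs.
- The article lists inclusion criteria only. Exclusions in the full protocol are not shown.

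These points limit the size, fix no direction for the bias and shape the remedy. They do not remove the problem. Physician confirmation establishes that rejection is present, not that it is new, and the stated definitions do not separate the two.

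**Conclusion.** The concern holds in a limited form. By the article's own rules, patients already in biopsy-proven rejection at the first ECG can enter and be counted in sensitivity, negative predictive value, the odds ratio and days to rejection. For those episodes the measures do not reflect early detection, because the onset could not be observed: the result is either a miss or a credit for an unrelated rise.

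The size is unknown. With true sensitivity of 77% and a prevalent share of 10 to 30%, observed sensitivity ranges from 54% (*f* = 30%, *q* = 0) to no change (*q* = 0.77). The reading rests on two assumptions: that the QTc rise accompanies the onset of rejection, and that some prevalent episodes persist, are confirmed and are counted. The article neither supplies *f* and *q* nor rules such cases out. Because the definitions can be repaired cheaply, this should be changed.

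**What to change.** Leave enrolment, the biopsy schedule and clinical care unchanged, and amend the definitions in Table 2:

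1. Classify each patient by the last biopsy on or before the first evaluable ECG: grade 0, grade 1R to 3R, or no biopsy yet.
2. Base the primary sensitivity, negative predictive value, odds ratio and days to rejection on episodes with onset after the first ECG. These are a first positive biopsy, a recurrence after a grade 0 biopsy, or a rise above the entry grade. The last keeps a 1R that progresses under monitoring.
3. Report prevalent episodes whose grade does not rise separately.
4. Report patients with no biopsy before the first ECG as a labelled category, because their status at that time is unknown.
5. Give the analysis of all episodes as a sensitivity analysis.

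No new data are needed: biopsy results are abstracted at each biopsy (Procedures), and episodes are collected from surgery (Follow-up and end-points). The cost is a few lines of definition and somewhat fewer episodes. If 20% of rejection patients left the primary analysis, 81.25 × 0.8 = 65 to 113.75 × 0.8 = 91 would remain. The half-width would widen from 9.2 to 10.2 points, or from 7.7 to 8.6 points.
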